## Background

Despite the modest gains from maternal and child healthcare interventions across the world, reproductive health issues remain a global challenge, particularly in developing countries. It is estimated globally that, more than 300,000 women died out of pregnancy or childbearing related conditions in 2015, with about 3 million neonatal deaths and 2.6 million stillbirths [1–4].

Among these figures exist a sharp disparity between and within countries. For example, stillbirth rates in Japan reduced from 18 per 1000 live births to 3 per 1000 live births between 1979 and 2010. In the United Kingdom, it was estimated that 1 in 200 pregnancies end in stillbirth [5–7].

Conversely, Nigeria alone, Africa’s most populous country recorded 42 per 1000 live births in 2015, which translated to over 300,000 babies dying before they are born [20, 21]. Albeit Ghana compares better to Nigeria, 28 per 1000 live births were also reported about the same period [8, 9]. In general, more than 98% of the world stillbirth estimates are accounted for by developing countries, particularly Sub-Saharan Africa and South Asia [10–13].

Recent studies have shown that quality antenatal care, during which time screenings are carried out on pregnant mothers to pick high-risk ones for target monitoring and management, can improve pregnancy outcomes and also minimize the risk of maternal morbidity and mortality [3, 14–16]. This principle holds for skilled delivery as well, often at a healthcare facility, where high-risk mothers and babies are managed using structured programs of emergency obstetric and neonatal intensive care [17, 18].

Nonetheless, country level and household income disparities exist widely across regions and have rather restricted access to maternal healthcare to the privileged, thereby stretching the inequality margin. Consequently, political leaders have introduced pro-poor policies as the panacea to bridging the access gap relative to maternal and child healthcare [19–22].

Within country policy interventions have ranged from equitable access to healthcare to the provision of quality healthcare at all levels for pregnant mothers and newborns [22–24]. In a similar vein, Ghana introduced one of such policies in 2008 dubbed, the ‘Free’ Maternal Healthcare Policy (FMHCP) with a primary aim of increasing facility delivery utilization and to achieve maternal and newborn care in general [3, 25, 26].

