## Specific objectives

To determine any significance in association between the FMHCP and antenatal care uptake, and facility delivery utilization in Ghana.To compare the difference in perinatal outcomes between Ghana and Kenya relative to the ‘free’ maternal health care policy.To measure the treatment effect of facility delivery on stillbirth, perinatal deaths, and neonatal mortality among women who received the FMHCP program compared to those who did not receive the program.To describe the ‘free’ maternal health care policy implementation in its current state in Ghana, within the context of funding constraints and implementation bottlenecks.

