### Exposure variables

The National Health Insurance status [proxy to the ‘free’ maternal healthcare policy (FMHCP)] is the main exposure variable. However, on the secondary level of analysis, antenatal care up-take (binary) and facility delivery utilization (also binary) are independent predictors, through which the secondary outcomes of interest; stillbirth, perinatal death, and neonatal death can be measured.

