### Covariates

Covariates are the moderating factors identified in the study conceptual framework. Covariates that show significant association with the variables of interest under consideration will be controlled for using multiple logistic regression. These include maternal characteristics such as; age, parity, pregnancy status, cesarean section, educational status, twin pregnancy, income level, abortion, and marital status. These will be adjusted for as confounding using logistics regression models. Population characteristics such as wealth index, distance, region, educational status, and rural/urban residence will also be adjusted for as confounding variables [42].

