### Data analysis

The secondary data will be cleaned and organized, dropping irrelevant variables and renaming covariates for ease of reference as necessary. Essentially, variables of interest in this study are binary outcomes i.e. 1 = case/the presents of an intervention, and 0 = no case, the absence of intervention, control.

Both multivariate logistic regression and Poisson with robust standard error, or negative binomial regression depending on whether there is over dispersion (conditional variance exceeding the conditional mean) will be fitted and analyzed. Thus, **loge** {*p*1 / *(1—pi)*} = *b0* + *b1 Xi1* + *b2 Xi2* + … + *bkXik*. The Use of the multiple logistic regression model also comes with the advantage of adjusting for confounding by including the covariates in the model.

For the matching method, Ghana’s DHS data sets (2008 and 2014) will be merged. This will increase the sample size to n = 8876, and add power to the study. The merger will also eliminate the risk of lack of common support, the so-called curse of dimensionality, a common phenomenon in propensity score matching, where treated units propensity scores cannot find suitable pairs.

Descriptive data will be presented using tables, frequencies, and proportions. The data will then be analyzed distinctly, using multiple statistical models and quasi-experimental design techniques. Firstly, the student independent *t*-test will be used to test for proportions, the significance of association, and mean differences between the independent variable, and the binary outcomes of interest; antenatal care uptake, and facility delivery utilization.

Test of association set < 0.05 less of significance, between the secondary variables of interest (stillbirth, perinatal death, and neonatal mortality) and the covariates; mothers age, marital status, level of education, wealth index, region, area of residence, twin delivery, parity, and employment status will be determined by using the Rao Scot Chis-square, which has an added sensitivity advantage, while adjusting for complex survey design features (weighting, clustering and stratification).

Only covariates found to be significantly associated with the dependent or independent variables will then be included in a multiple logistic regression model and adjusted for confounding [72].

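### The facility-delivery effect on deaths is open to confounding by antenatal care, which is in no covariate list in the visible text, unless both enter one model

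*Protocol article*

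**What the plan says.** The third specific objective is: "To measure the treatment effect of facility delivery on stillbirth, perinatal deaths, and neonatal mortality among women who received the FMHCP program", compared with women who did not receive it. Hypotheses 2 and 3 put the same exposure against perinatal deaths.

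Under Exposure variables, at the secondary level of analysis, "antenatal care up-take (binary) and facility delivery utilization (also binary) are independent predictors" for stillbirth, perinatal death and neonatal death. The text does not say whether the two enter one model or two.

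Adjustment is described in two places:

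- **Covariates.** The maternal list is "age, parity, pregnancy status, cesarean section, educational status, twin pregnancy, income level, abortion, and marital status". The second list reads: "Population characteristics such as wealth index, distance, region, educational status, and rural/urban residence will also be adjusted for as confounding variables". Both are introduced as examples, so they are open.
- **Data analysis.** The covariates to be tested against the three death outcomes are "mothers age, marital status, level of education, wealth index, region, area of residence, twin delivery, parity, and employment status". This list is closed, and an entry rule follows: "Only covariates found to be significantly associated with the dependent or independent variables will then be included in a multiple logistic regression model".

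None of these lists contains antenatal care. For matching, the Data analysis section refers only to controlling for the confounding variables and names none.

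The Background describes antenatal care as the time when "screenings are carried out on pregnant mothers to pick high-risk ones for target monitoring and management", and says that good antenatal care can improve pregnancy outcomes. Table 5 already derives the binary variable anc4 from m14.

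**The concern.** Antenatal visits come before the birth. On the protocol's own premise they can affect the outcome. If women with 4+ visits are also more likely to deliver in a facility, antenatal care is a common cause of exposure and outcome, and leaving it out credits part of its benefit to the place of birth.

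This touches the central mortality question. The distortion would favour facility delivery, which is the direction that the Expected outcome section anticipates, so the result would not look suspicious. It would also be avoidable: propensity score matching already has to assume that unobserved characteristics are balanced, and here an observed and already coded variable is left out.

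**Working it through.** **Step 1: can antenatal care reach the facility-delivery model?**

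| Route | Does it bring antenatal care in? |
|---|---|
| Covariates section, maternal list | Not named (open list) |
| Covariates section, population list | Not named (open list) |
| Data analysis list for the death outcomes | Not named (closed list) |
| Entry rule | Admits only screened covariates; antenatal care is not among those screened |
| Matching | Refers back to the confounders without naming them |
| Joint regression with both predictors | Yes, if that is what is meant |

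Only the last route works, and the text does not commit to it. It is also not available in a propensity score with facility delivery as the single treatment.

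**Step 2: size of the bias.** The plan states no figure that bears on this, so there is none to reproduce. All inputs are assumptions, taken within strata of the listed covariates:

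- P(A), the share with 4+ visits: 0.55 to 0.75
- facility delivery with 4+ visits, f1: 0.60 to 0.80
- facility delivery with fewer visits, f0: 0.35 to 0.40
- antenatal risk ratio on death, r: 0.7 to 0.8, with 0.5 as a strong case
- true facility risk ratio: 1.0

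With F = facility and H = not in a facility:

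- P(A|F) = P(A)·f1 / [P(A)·f1 + (1 − P(A))·f0]
- P(A|H) = P(A)·(1 − f1) / [P(A)·(1 − f1) + (1 − P(A))·(1 − f0)]
- apparent facility RR = [P(A|F)·r + 1 − P(A|F)] / [P(A|H)·r + 1 − P(A|H)]

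*Middle case*: P(A) = 0.75, f1 = 0.70, f0 = 0.35, r = 0.7.
- P(A|F) = 0.525 / (0.525 + 0.0875) = 0.857
- P(A|H) = 0.225 / (0.225 + 0.1625) = 0.581
- RR = (0.857·0.7 + 0.143) / (0.581·0.7 + 0.419) = 0.743 / 0.826 = 0.90

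*Largest bias in the range*: P(A) = 0.55, f1 = 0.80, f0 = 0.35.
- P(A|F) = 0.44 / 0.5975 = 0.736; P(A|H) = 0.11 / 0.4025 = 0.273
- r = 0.7: 0.779 / 0.918 = 0.85
- r = 0.5: 0.632 / 0.863 = 0.73

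*Smallest bias in the range*: P(A) = 0.75, f1 = 0.60, f0 = 0.40, r = 0.8.
- P(A|F) = 0.45 / 0.55 = 0.818; P(A|H) = 0.30 / 0.45 = 0.667
- RR = 0.836 / 0.867 = 0.965, about 0.97

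*Weak link*: P(A) = 0.80, f1 = 0.60, f0 = 0.50, r = 0.8 gives 0.98. With f1 = f0 the result is exactly 1.00.

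**Step 3: the joint model.** With both predictors in one regression, the facility coefficient is adjusted for antenatal care and this bias goes. The antenatal coefficient then leaves out whatever passes through facility delivery. With f1 = 0.70, f0 = 0.30, a direct antenatal RR of 0.8 and a facility RR of 0.8, the model shows 0.80, while the total antenatal effect is 0.8 × (0.70·0.8 + 0.30) / (0.30·0.8 + 0.70) = 0.8 × 0.86 / 0.94 = 0.73.

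**The case against.** **Antenatal care is a named predictor, so its absence from a covariate list is natural.** This stands in part. If the two predictors share one regression, the facility estimate is already adjusted for antenatal care. But the text does not say so, and a propensity score for facility delivery would still omit it.

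**Adjustment sets belong in the full protocol or analysis plan.** This would hold if the article were silent. It is not: it gives a closed list for the death outcomes and a rule that only screened covariates enter.

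**Hidden figures and open lists.** The Covariates section refers to the conceptual framework (Figure 1), and Figure 3 is captioned as showing confounders. Neither is shown, and the lists in that section are open. So the absence is established for the visible text only.

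**The Background does not say that antenatal care leads to facility delivery.** Correct; that link is an assumption here. If screening sends high-risk women to facilities, the estimate is also pushed the other way, and a 4+ visit indicator would not correct that, because it does not measure risk.

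**A stronger reading.** A reader might infer that both model choices are equally damaging, or that a joint model would report a real antenatal benefit as no effect. The documents do not support this. No objective, research question or hypothesis asks for the effect of antenatal care on deaths. A null antenatal coefficient would require antenatal care to act only through facility delivery; with any direct effect, part of it remains visible.

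**Conclusion.** The concern holds for the facility-delivery estimate in separate regressions, and in any propensity score with facility delivery as the treatment. Under the assumed inputs, a null effect on deaths would read as a risk ratio of about 0.85 to 0.97 for an antenatal risk ratio of 0.7 to 0.8, and as low as about 0.73 for one of 0.5. This rests on an association between antenatal care and facility delivery within covariate strata that the protocol does not quantify; without that association there is no bias. A joint regression would be sound for objective 3. The reading of the antenatal coefficient in such a model is a matter of labelling only. The change should be made, because it concerns the main mortality question and the variable already exists.

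**What to change.** - In every regression of a death outcome on facility delivery, include antenatal care (m14 or anc4) as a fixed covariate, exempt from the significance screen.
- Include it in the propensity score wherever facility delivery defines treatment. The Operational definitions also allow 4+ visits to define treatment; there it cannot be a matching covariate, so state which definition each matching analysis uses.
- Say whether the two predictors enter one model. If they do, label the antenatal coefficient as the part of its effect that does not pass through facility delivery. If the total antenatal effect is wanted, leave facility delivery out of that model.

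The cost is a few sentences, plus a rule for records with a missing visit count. Confounding by obstetric risk would remain and should be stated as a limitation.

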### Outcome variables

Antenatal care uptake and facility delivery utilization are the primary outcomes of interest. However, on the secondary level of analysis for the FMHCP impact, stillbirth, perinatal death, and neonatal mortality are the secondary outcomes variables, to determine the policy effect.

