## Operational definitions

*Utilization*: The use of maternal healthcare services rendered in a healthcare facility at any level.

*Maternal healthcare*: Antenatal care clinics and facility delivery services provided to pregnant women in a healthcare facility.

*Antenatal care uptake*: This refers to a 4+ antenatal care visit, thus, antenatal clinic visits of less than 4 are equal to zero visits (or 'no visit').

*Facility delivery*: This is when a pregnant woman gives birth in a healthcare facility at any level.

*Stillbirth*: This refers to the birth of a fetus with no signs of life, after 28 weeks of gestation or the death of a fetus within 24 h after birth.

*Perinatal death*: This refers to the number of stillbirth plus the death of neonates within the first week of life.

*Neonatal deaths*: This refers to the number of newborn deaths within 28 days of life.

*Treatment group*: Pregnant women study participants registered with the national health insurance scheme and made 4+ antenatal care visits or pregnant women participants in Ghana who delivered in a healthcare facility.

*Comparison group*: Pregnant women study participants registered with the national health insurance but have made less than 4 antenatal care visits with less than four minimum antenatal visits or pregnant women who did not deliver in a healthcare facility within the study period.

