### Variables of interest

The maternal healthcare utilization examines two primary outcome variables which include; antenatal care up-take (4+ visit = 1, and ≤ 3 visits = 0), and facility delivery utilization, also binary outcome (facility delivery = 1 and home delivery = 0). Mothers’ health insurance status (proxy to the FMHCP) is the exposure variable of interest in this study.

Stillbirth, perinatal death, and neonatal mortality are secondary outcome variables of interest generated as binary outcomes from the DHS data sets using variable *b6,* and *b7* against which the policy utilization impact will be measured. Table 5 presents the derived variables generated using STATA 15.0 from the 2008/2014 DHS data sets.

**Table 5 Tab5:** Variables of interest

Item	Label	Name	Recoding	Binary V
1	Respondent holds valid NHIS card	*S1015*	Holds a valid NHIS card (with or with no evidence) = 1 No valid NHIS card = 0	*Vid_1*
2	Respondent hold valid NHIS card	*S1015*	Holds a valid NHIS card (with evidence) = 1 No valid NHIS card plus (holds a valid NHIS card with no evidence) = 0	*Vid_2*
3	Number of ANC visit during pregnancy	*m14*	Antenatal visits 0–3 = 0 Antenatal visits ≥ 4 = 1	*anc4*
4		*m15*	Home delivery = 0 All facility delivery = 1	*fdelivery*
5	Age at death	*b6*	Alive after day 0 = 0 Born dead/died on day 0 = 1	*stillbirth*
6	Age at death	*b6*	Did not die before 7th day = 0 Died before 7th day of life = 1	*prdeaths*
7	Age at death (months imputed)	*b7*	Did not die before 28th day = 0 Died before 28th day of life = 1	*neodeaths*

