Logistics regression is considered appropriate, giving the binary status variables of interest; antenatal care up-take [yes = 1 (ANC visit ≥ 4)] and [no = 0 (ANC visit of ≤ 3]; facility delivery utilization [yes = 1 (facility delivery) and no = 0 (home delivery)], and the secondary outcome variables; stillbirth, perinatal and neonatal deaths, generated through the re-coding of the relevant variable *m14, m15, b6, b7*, and *s1015,* from the DHS data sets (Table 5).

The treatment difference will be determined through nearest-neighbor matching of treated and untreated units’ propensity scores generated ex-post, and using logistics regression while controlling for the confounding variables for precision. The 'free' policy impact will then be determined using the average treatment effect on the treated. Robustness of results will be achieved with reduced standard errors using bootstrapping replication while testing for sensitivity using a t-test of bias, and probit regression.

Of the treatment and comparison country analysis, the DID analysis will be used to determine the policy impact, using the 2008 data set of the two countries (Ghana and Kenya) as a baseline and 2014 data sets as the end line. The study is powered by the sample size calculation, originally determined by the survey design. The sample size is n = 2992/5884 (8,876) for Ghana DHS 2008/2014 data sets, and n = 6079/20,964 (27,043) for Kenya DHS 2008/2014 data sets respectively.

Clustering and stratification will be adjusted for using sample survey weighting at all stages of the analysis. This will produce unbiased treatment estimate that can be generalized to the original survey population [26, 52].

The qualitative data will be deductively analyzed using predefined themes. However, common themes that emerges from the interviews and focused discussion will be organized as sub-themes and inductively reported. The approach will be aided by NVIVO 12, through which nodes and their children will be created to categories significant statements into similarities and dissimilarities [73].

The results of the primary data will be reported using the common themes approach with word frequency count and cloud, and vivid quotations to back themes. The inclusion of qualitative data will add context and situate the discussion with explanatory power to the statistical findings [48].

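### The plan allows the difference in deaths between facility and other births to be reported as the policy effect, although that contrast measures place of birth

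*Protocol article*

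**What the plan says.** Several sections of the protocol article bear on what the death analysis estimates.

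- **Outcome variables**: at the secondary level of analysis, stillbirth, perinatal death and "neonatal mortality are the secondary outcomes variables, to determine the policy effect". **Variables of interest** describes the same deaths as outcomes "against which the policy utilization impact will be measured".
- **Exposure variables**: insurance status, the proxy for the policy, is the main exposure. At the secondary level, however, "antenatal care up-take (binary) and facility delivery utilization (also binary) are independent predictors" of the deaths.
- **Operational definitions**: the second limb of the treatment group is "pregnant women participants in Ghana who delivered in a healthcare facility". The matching limb of the comparison group is "pregnant women who did not deliver in a healthcare facility within the study period".
- **Data analysis**: the treatment difference comes from nearest-neighbour matching, and the "policy impact will then be determined using the average treatment effect on the treated" (ATT). The same section also assigns the policy impact to the Ghana-Kenya, 2008-2014 DID.
- **Specific objectives**: the third objective is "To measure the treatment effect of facility delivery on stillbirth, perinatal deaths, and neonatal mortality among women who received the FMHCP program", compared with women who did not receive it. The second objective compares perinatal outcomes between the two countries.
- **Study design**: the matched groups are 2014 births (treated) and 2008 births (untreated).

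**The concern.** A contrast between facility and non-facility births answers the question of what place of birth does to the risk of death. The policy question is what happened to deaths because the policy existed. Through facility delivery, the policy can change the outcome only for births it moved into a facility.

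Research question 2 and the second and third hypotheses set the facility contrast among women who all received the policy. Policy exposure then does not differ between the two arms, so their difference would be the same if the policy had moved no births at all.

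The missing term is the policy-induced change in facility delivery. The study estimates it as a primary outcome, but nothing in the article links it to the death contrast. The Discussions section plans projections of stillbirth and perinatal death against SDG 3, and the Expected outcome section anticipates changes to the policy. Both would be misdirected if a place-of-birth difference stood in for the policy's effect.

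**Working it through.** **No plan figure to reproduce.** The article states no policy effect on deaths, no facility-delivery rate and no policy-induced rise in facility delivery. Its sample sizes do add up: 2992 + 5884 = 8876 for Ghana and 6079 + 20,964 = 27,043 for Kenya.

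**Notation**
- RD: risk of death in facility births minus risk in non-facility births (size only below).
- P1: share of births in facilities under the policy.
- d: share of all births that the policy moved into facilities, so the share without the policy is P1 - d.

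**Assumptions**: RD is causal, and it is the same for moved and unmoved births.

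**Step 1, all births.** Mean risk is (facility share) x (facility risk) + (1 - facility share) x (non-facility risk). Moving the share from P1 - d to P1 changes it by d x RD. The contrast divided by the policy effect is RD / (d x RD) = 1/d.

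**Step 2, facility births only.** This is the population of an ATT when treated means born in a facility. A fraction d/P1 of these births was moved, so the policy effect among them is (d/P1) x RD and the ratio is P1/d.

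**Step 3, numbers.** d and P1 are assumed ranges; neither is in the article.

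| d | All births, 1/d | Facility births, P1 = 0.6 | P1 = 0.7 | P1 = 0.8 |
|---|---|---|---|---|
| 10% | 10.0 | 6.0 | 7.0 | 8.0 |
| 15% | 6.7 | 4.0 | 4.7 | 5.3 |
| 20% | 5.0 | 3.0 | 3.5 | 4.0 |
| 25% | 4.0 | 2.4 | 2.8 | 3.2 |

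The ratio does not depend on RD. It shrinks when the policy moved many births: at d = 50% it is 2.0 over all births, and at d = 40% with P1 = 0.7 it is 1.7 over facility births.

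**Step 4, illustration.** Take an assumed RD of 10 per 1000 and the Ghana 2008 neonatal rate of 30 per 1000 (Kenya as a comparison country). The contrast looks like 10/30 = 33% of baseline. With d = 10%, the policy effect through this route is 0.10 x 10 = 1 per 1000 over all births, or 1/30 = 3.3%. With d = 0 it is zero, whatever the contrast shows.

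**The case against.** The strongest reply is that no single sentence of the article orders this analysis. The Outcome variables section names no exposure, and its wording would also fit the insurance proxy or the DID. Study design defines the matched groups by survey year, and on that definition the ATT is a period contrast to which neither factor applies. The objectives, research questions and hypotheses mostly call the quantity an effect of facility delivery, and the DID is already planned for the policy impact.

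Much of this stands, and it limits the point. It does not remove it. The Exposure variables and Outcome variables sections describe the same secondary level: one supplies facility delivery as predictor, the other calls the result the policy effect. Research question 3 asks for a treatment difference of facility delivery, and Data analysis uses the same term for what matching estimates just before calling the ATT the policy impact. Operational definitions supports that reading and Study design contradicts it. An analyst could follow either.

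A reader might infer three stronger things that the document does not support:

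- **That a stated policy impact on deaths is several times too large.** No such figure is stated, and the factor cannot be fixed without d and P1.
- **That every policy estimate in the study is affected.** The DID and the 2014 versus 2008 matching carry no such factor.
- **That the reported contrast must err upwards.** The Background says that high-risk mothers are managed in facilities. Residual confounding by risk could shrink or reverse the observed difference.

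**Conclusion.** The point holds in this form: the article permits a facility versus non-facility difference in deaths to be reported as the policy effect, and its definitions of treated and comparison conflict. The facility contrast and the policy effect are different quantities even under perfect adjustment.

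The size is conditional. If the contrast is causal and equal for moved and unmoved births, it exceeds the policy effect through facility delivery by the factors tabulated above, namely 10 to 4 (all births) or about 8 to 2.4 (facility births) for the assumed d of 10-25% and P1 of 0.6-0.8. These factors describe the mislabelling alone. They cover only the facility route; antenatal care is a second route that the plan names, so d x RD is not the whole policy effect.

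**What to change.** 1. In Outcome variables and Data analysis, state that the policy effect on each death outcome is the Ghana-Kenya, 2008-2014 DID on all births, as the second objective already implies.
2. Report the facility versus non-facility contrast as an effect of, or association with, facility delivery. Do not call it policy impact.
3. Reconcile the treatment and comparison groups in Operational definitions with those in Study design and in Statistical methods and rationale, so that each analysis has one stated definition of treated.
4. Optional: if a figure through facility delivery is wanted, report (DID change in facility delivery) x (facility minus non-facility death difference), with an interval from a bootstrap over primary sampling units. State the equal-effect assumption and that the figure omits the antenatal care route.

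Steps 1 to 3 need only wording and no new data; step 4 adds one derived estimate. The price is that the reported mortality impact will be smaller or less precise. As a rough guide, a simple before-after comparison in Ghana alone (2992 v 5884, from 30 per 1000, ignoring clustering) has power of about 82% for a fall of 10 per 1000 but about 10% for a fall of 2.5 per 1000. The DID also carries Kenya's sampling error.
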